## Abstract

**Background:**

The use of thermal ablation of liver tumors is rapidly increasing. This is despite a lack of high-level evidence of the oncologic efficacy of ablation. Ablation is most often used in cases where resection is not possible, but as the technique has improved it is increasingly used as a substitute for resection.

**Patients and Methods:**

New Comet is an international multicenter randomized controlled double-blinded, non-inferiority trial comparing thermal ablation to resection of colorectal liver metastases. It will include 230 patients with colorectal liver metastases (up to 5 lesions, tumor size up to 3 cm) where thermal ablation and resection both are considered suitable treatment options for all lesions. The patients are randomized to either resection or ablation, and all lesions in each patient are treated with the same modality. Complete ablation will be verified with intraoperative computed tomography and ablation confirmation software.

**Conclusions:**

The primary endpoint is local tumor recurrence at 12 months. Secondary endpoints include overall survival, disease-free survival, time to surgical failure, health-related quality of life, complications, and cost-effectiveness (trial registration no.: NCT05129787).

**Supplementary Information:**

The online version contains supplementary material available at 10.1245/s10434-025-17984-5.

Colorectal cancer is on the rise in the Western world, with 160,000 new cases and a 2% annual increase in people under 50 years in the USA.^1^ Low- and middle-income countries also see an increase in colorectal cancer cases, increasing the global burden of this disease.^2^ The liver is the dominant site for colorectal cancer metastases. Long-term survival after surgery for colorectal liver metastases has improved dramatically, from less than 40% 5-year survival in the 1980s to more than 55% in recent reports.^3,4^ This improvement is related to advances in oncologic treatment, better preoperative diagnostics and patient selection, improved perioperative care and surgical equipment, and better anatomic and physiological understanding of the liver. Minimally invasive treatments now allow some patients to leave the hospital on the first day after surgery, without any detriment in oncologic outcomes.^5^

As more patients survive stage 4 colorectal cancer, the focus on reducing side effects of treatment has increased. Our group have previously shown that laparoscopic liver surgery improved patient’s postoperative quality of life compared with open liver surgery.^6^ In parallel, even less invasive treatments of liver tumors have emerged, such as thermal ablation.

A 2019 systematic review reaffirmed surgical resection as the gold standard for the treatment of colorectal liver metastases, concluding that resection should not be replaced by thermal ablation.^7^ In most published studies, ablation was associated with inferior oncologic outcomes compared with resection. However, the authors noted that these findings are often confounded by selection bias, as patients undergoing ablation were typically those with poorer prognostic factors; either deemed unresectable or too frail to undergo resection.

The use of ablation of liver tumors is rapidly increasing worldwide.^8,9^ This is despite a lack of high-level evidence of the oncologic efficacy of ablation of colorectal liver metastases. Ablation is most often used in cases where resection is not possible, but as the technique has improved it is increasingly used as a substitute for resection.^10^ The European multicenter prospective cohort trial MAVERRIC showed that microwave ablation performed in high-quality centers could lead to similar overall survival as surgical resection in small resectable colorectal liver metastases.^11^

The randomized controlled multicenter COLLISION trial was recently published.^12^ COLLISION was a noninferiority trial including 300 patients with 1–10 target colorectal liver metastases, defined as tumors that were considered both ablatable and resectable. The trial also included patients who had additional nontarget lesions that were only suited for one treatment modality, and approximately 27% of the patients in the trial were treated with a combination of resection and ablation. The primary endpoint of COLLISION was overall survival (OS), and OS following ablation was noninferior to that following resection. Local recurrence (frequently defined as new tumor tissue adjacent to the ablation zone or resection bed) was per patient 14% after resection and 12% after ablation. The local recurrence result was surprising to many, given that previous studies have reported local recurrence after surgery as low as 4%.^13^

Local recurrence after ablation is often related to incomplete ablation. Ablation confirmation software can improve the evaluation of ablation zones.^14^ The software uses co-registration of pre- and post-ablation computed tomography (CT) scans to illustrate how the ablation zone covers the tumor in all planes. Used intraoperatively it can increase precision when performing re-ablation by identifying inadequate margins. In the COLLISION trial ablation confirmation software was recommended, but not mandatory.

New Comet will be the first randomized trial to compare ablation alone with resection alone in patients with colorectal liver metastases. It will also be the first trial to use confirmation software in all ablation patients to optimize ablation margins where possible.

## Patients and Methods

### Study Design

New Comet is a multicenter randomized controlled trial. The study is powered to determine whether thermal ablation of colorectal liver metastases is non-inferior to resection with regard to local tumor recurrence at 12 months.

This is an ongoing trial at Oslo University Hospital (principal investigator, Oslo, Norway), Karolinska University Hospital (Stockholm, Sweden), University Hospital of North Norway (Tromsø, Norway), and Sahlgrenska University Hospital (Gothenburg, Sweden).

### Endpoints

#### Primary Endpoint

The primary endpoint of the trial is local tumor progression within 12 months. Local tumor recurrence is defined as new tumor tissue adjacent (0 mm distance) to the resection margin or ablation zone at the first imaging where the new tumor is visible.

#### Secondary Endpoints

Overall survival (OS)
The main analysis will be on intention-to-treat (ITT) basis.A secondary OS analysis will be performed on an oncological homogenous group of patients with the following requirements:no previous surgical procedure on the liverno extrahepatic metastasesprimary tumor resectedDisease-free survival and liver-specific disease-free survivalTime to surgical failure^15^Local tumor recurrence at 24 monthsPostoperative complicationsHealth-related quality of lifeCost-effectivenessTime to functional recoveryInflammatory responseIntraoperative circulation physiologyEvaluation of liver movement in different ventilation modesMinimum ablative margin needed to prevent local tumor recurrenceEffect of blinding on patient-reported postoperative outcomes and hospital stay

The New Comet trial has multiple substudies, illustrated in Fig. 1.

**Fig. 1 Fig1:**
[figure not shown]
New Comet trial: overview of substudies; *RAND-36* RAND-36 Measure of Health-Related Quality of Life, *p.o.* postoperative; *HLQ* health literacy questionnaire, *AI* artificial intelligence

### Study Population

Patients referred for surgical treatment of colorectal cancer liver metastases to participating hospitals will be discussed in a multidisciplinary team with respect to surgical strategy. The trial will only include patients in whom all liver metastases can safely be treated with both modalities (either ablation only or resection only). Full inclusion and exclusion criteria are listed in Table 1.

**Table 1 Tab1:** Inclusion and exclusion criteria

Inclusion criteria	Exclusion criteria
Histologically verified colorectal cancer. Colorectal liver metastases (proven or suspected) eligible for radical treatment using EITHER resection OR ablation (not a combination), as decided by the liver MDT meeting at the study center. Patient is fit to undergo both resection and ablation of all liver metastases. Size of largest lesion up to and including 30 mm. In case of solitary metastasis, resection plan includes resection of ≤ 2 anatomical segments. In case of multiple metastases in one continuous resection, resection plan can include ≤ 4 anatomical segments (including hemihepatectomy). ≤ 5 tumors to be treated in one procedure. Primary tumor either resected (primary first) or with a plan for curative treatment (liver first). Age ≥ 18 years.	More than 3 lung metastases. If solitary lung metastasis, size > 15 mm. If 2–3 lung metastases, size > 10 mm. (OR: unresectable lung metastases as decided by the lung MDT meeting). Presence of extrahepatic, extrapulmonary metastases. Surgical indication for removal of enlarged lymph nodes in the hepatic hilum. (Enlarged lymph nodes without indication of removal are not considered an exclusion criterium). Tumor closer than 10 mm to right/left main bile duct. Suspected tumor infiltration to adjacent organs. Progression (as of RECIST^25^) on second-line chemotherapy. Vanished lesions following neoadjuvant chemotherapy (Exception: Lesions with complete response to neoadjuvant chemotherapy; defined as no recurrence of lesion within 1 years after vanishing, including a chemo-free interval of at least 3 months). Previous inclusion in this trial. Not eligible for workup according to study criteria. Contraindication to contrast enhanced CT scan. Manifest liver cirrhosis with Child–Pugh score ≥ B7. Pregnancy. ECOG performance status ≥ 3. Simultaneous resection of primary tumor or any other concomitant surgical procedure, with the exception of cholecystectomy. Need for liver volume expansion. Any other reason why, in the investigator’s opinion, the patient should not be included.

MDT, multidisciplinary team; RECIST, response evaluation criteria in solid tumors; CT, computed tomography; ECOG, Eastern Cooperative Oncology Group

### Preoperative Workup

All patients will undergo standardized radiological workup before inclusion, consisting of contrast-enhanced X-ray computed tomography (CT) scans of the chest and abdomen, and magnetic resonance imaging (MRI) of the liver enhanced with liver-specific contrast agent. The last CT or MRI of the liver taken before randomization must not be more than 5 weeks old at the date of surgery.

### Randomization

Randomization will be electronically performed after all neoadjuvant treatment is administered if applicable, inclusion and exclusion criteria are controlled, and informed patient consent has been obtained. The patients will be allocated to treatment with resection or ablation with an allocation ratio of 1:1. A dedicated electronic randomization software has been created using block randomization with variable block sizes and stratified randomization to ensure similar numbers of the following prognostic factors in both groups:Size of largest tumor over 2 cm.Superficial lesion (no visible liver tissue between tumor and liver surface on preoperative radiology).Treatment center.

### Sample Size Calculation

Ablation has previously been associated with high local recurrence rate, up to 20%, compared with 2–3% for resection.^13^ Recent analyses of ablation using modern techniques for needle guidance and ablation zone confirmation report local recurrence as low as 4%.^14^

In this trial we expect a local recurrence rate of 2% in the resection group (control) and 7% in the ablation group (intervention). Given that ablation has frequently been used despite expected local recurrence numbers of up to 20%, we consider a non-inferiority margin of 13% acceptable. With a two-sided alpha of 5% and a power of 80%, 208 patients are needed to exclude a difference in favor of the resection group of more than 13 percentage points (equaling a local recurrence percentage of 2% following resection and 15% following ablation). To allow for 10% dropout we aim to include 230 patients in total, 115 in each group.

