#### Statistical Analysis

The primary outcome of local tumor recurrence within 12 months after study intervention will be analyzed with a Kaplan–Meier plot, a log-rank test for equality of survival curves, and a Cox proportional hazard regression model. The primary analysis will be the Cox regression model, and we will report the estimated hazard ratio (HR) with a 95% confidence interval for thermal ablation versus surgical resection and a p-value for the null hypothesis of no treatment difference (HR 1). The median survival time in each treatment group will be estimated with the Kaplan–Meier estimator and presented with 95% confidence intervals. The outcomes of disease-free and overall survival will be analysed and reported in the same manner as the primary outcome.

Continuous outcomes measured at one time point (i.e. at 12 months) will be analysed with two-sample *t*-test, with adjustments for unequal variances (the Welch *U* test), and 95% confidence interval for the difference between means. In cases where the distribution of the outcome is considerably skewed, median regression will be used and differences in medians instead of means will be analyzed.

Change in continuous outcomes measured at baseline and 12 months will be analyzed with analysis of covariance (ANCOVA), i.e., a linear regression model where the 12 months measurement is the dependent variable and treatment and baseline measurement are the independent variables. The between-treatment difference in change from baseline will be estimated with a 95% confidence interval, and a *p*-value for the null hypothesis of no treatment difference.

Dichotomous variables will be analyzed with Fisher mid-*p* tests and Newcombe hybrid score confidence intervals.^18^ Ordered categorical variables with more than two categories will be analyzed with Wilcoxon–Mann–Whitney tests (score tests for effect in a proportional odds model).^19^ A statistical analysis plan will be prepared and published at clinicaltrials.gov.

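### At about 2 and 7 expected events, 208 patients do not give 80% power at the stated 5% alpha: risk-difference intervals that hold the error give about 65%

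*Protocol article*

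**What the plan says.** All the design inputs are in the Protocol article, section Sample Size Calculation. The expected rates are given as "we expect a local recurrence rate of 2% in the resection group (control) and 7% in the ablation group (intervention"). The margin is absolute: "we consider a non-inferiority margin of 13% acceptable", with the boundary case spelled out as "equaling a local recurrence percentage of 2% following resection and 15% following ablation". The conclusion is "With a two-sided alpha of 5% and a power of 80%, 208 patients are needed". A 10% dropout allowance brings the target to 230, or 115 per arm. The Randomization section sets the arms "with an allocation ratio of 1:1". No formula or test is named beside the 208.

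The Statistical Analysis section names a Cox model as the primary analysis, reported as a hazard ratio with a 95% interval and a p-value against HR 1. For dichotomous variables in general, it names Fisher mid-p tests and "Newcombe hybrid score confidence intervals". That is the only interval for a difference in proportions in the document, and it is not tied to the primary outcome.

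**The concern.** The sample size rests on a difference of two small proportions. At 104 per arm the plan expects 104 × 0.02 = 2.1 recurrences after resection and 104 × 0.07 = 7.3 after ablation. With so few events, the estimated standard error of a Wald interval varies strongly with the observed counts, so its nominal error rate and formula power may both be off.

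The stake is the reliability of the non-inferiority conclusion. If the margin is tested with an interval that keeps its error rate, the chance of missing non-inferiority under the trial's own assumptions is higher than the stated one in five. If a Wald interval is used to stay near 80%, the chance of declaring non-inferiority when ablation is truly 13 points worse exceeds 2.5%.

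**Working it through.** **Inputs** (Sample Size Calculation; Randomization for the ratio): resection 2%, ablation 7%, margin 13 points, two-sided alpha 5% (one-sided 2.5% for non-inferiority), power 80%, allocation 1:1.

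**Step 1: reproduce 208.** Unpooled normal formula, per arm:

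n = (z₀.₉₇₅ + z₀.₈₀)² × [p₁(1 − p₁) + p₂(1 − p₂)] / (margin − (p₂ − p₁))²

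= (1.96 + 0.8416)² × (0.02 × 0.98 + 0.07 × 0.93) / (0.13 − 0.05)²

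= 7.849 × 0.0847 / 0.0064 = 103.9, so 104 per arm and 208 in total. This matches the plan. Formula power at 104 per arm is 80.05%.

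**Step 2: exact power and error.** For every pair of event counts (x resection, y ablation), compute the upper 95% limit of ablation minus resection and count success if it is below 0.13. Sum Binom(x; n, p₁) × Binom(y; n, p₂) over the successes. Power uses 2% and 7%. Type I error uses the plan's own boundary case, 2% and 15%.

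| Interval, 104 per arm | Power (2% vs 7%) | One-sided type I error (2% vs 15%) |
|---|---|---|
| Wald | 78.1% | 4.1% |
| Newcombe | 64.7% | 2.1% |
| Miettinen-Nurminen | 64.7% | 2.1% |

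A simulation with standard software gave 78.1% for Wald and 64.3% for Newcombe, which agrees.

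**Step 3: all 230 evaluable (115 per arm).** Newcombe gives 70.8% and Miettinen-Nurminen 68.6%. Zero dropout therefore does not restore 80%.

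**Step 4: where the gap comes from.** With 2 resection events at 104 per arm:

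- 8 ablation events: upper limit 11.5 points (Wald) and 12.7 (Newcombe). Both succeed.
- 9 ablation events: 12.7 (Wald) and 13.8 (Newcombe). Only Wald succeeds.

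For 1 to 5 resection events, Newcombe allows one ablation event fewer than Wald. When only about 7 are expected, one event moves the power by more than ten points.

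**Step 5: sensitivity to the 7%.** Newcombe power at 104 per arm with 2% after resection:

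| Ablation rate | Power |
|---|---|
| 5% | 88.9% |
| 5.8% | 80.6% |
| 6% | 78.1% |
| 7% | 64.7% |
| 8% | 50.3% |

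The stated 80% is reached only if the ablation rate is about 5.8% or lower.

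**The case against.** The strongest reply is that nothing was miscalculated. The 208 follows from a common formula, and the exact power of the matching Wald test, 78.1%, is close to 80%. That stands: a reader might infer an arithmetic error, and there is none. What the reply leaves out is alpha. Wald reaches 78% with an error of 4.1% instead of 2.5%.

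Second, a reader might take 65% as the power of the planned primary analysis, or as an unconditional one-in-three risk of failure. The document does not support that. It names a Cox model for the primary outcome and Newcombe only for dichotomous variables in general. The 65% applies if the 13-point margin is tested with a risk-difference interval that holds its error. Equally, the Cox model does not rescue the 80%, because a test against HR 1 does not address a 13-point margin. As a rough guide, assume proportional hazards. The margin then becomes HR ln(0.85)/ln(0.98) = 8.0 and the expected HR is ln(0.93)/ln(0.98) = 3.6. With about 7.3 and 2.1 events, SE(log HR) ≈ √(1/7.28 + 1/2.08) = 0.79, which gives about 18% power.

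Third, the choice of interval can be left to the statistical analysis plan, which the article says will follow. That is fair, and the missing assignment of an interval is not the fault raised here. The 80% claim, however, is made in this document. Nor does the shortfall depend on picking Newcombe, since Miettinen-Nurminen gives the same power.

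Fourth, doubt about the 7% matters at least as much as the interval, as Step 5 shows. This also stands.

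Finally, a reader might see further proof in the resection rates. The Sample Size Calculation contrasts ablation and resection as "up to 20%, compared with 2–3% for resection", while the introduction, citing the same reference, says "previous studies have reported local recurrence after surgery as low as 4"%. Neither place gives the unit or time point of the figure, and the source is not available here. This is a separate citation query and has no bearing on the power at 2% versus 7%.

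**Conclusion.** The point holds in conditional form. The 208 is the right answer from the Wald formula, but at these event rates the stated alpha and power do not hold together. Wald gives 78% power with 4.1% one-sided error. Newcombe and Miettinen-Nurminen give about 65% with 2.1% error, a shortfall of about 15 points. Under the plan's assumptions the chance of missing non-inferiority is then about 35% rather than 20%. With all 230 evaluable, Newcombe gives about 71%.

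The result rests on true rates of exactly 2% and 7%, binomial outcomes at 12 months with complete status in the evaluable patients, a two-sided 95% interval, and a risk-difference test of the 13-point margin.

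**What to change.** State that non-inferiority is judged by the upper limit of the two-sided 95% Newcombe (or Miettinen-Nurminen) interval for the 12-month difference, ablation minus resection, against 13 points. Make clear that the Cox hazard ratio does not carry the non-inferiority test.

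Restate the power, with Newcombe, as about 65% with 208 evaluable and about 71% with 230 evaluable, or as 80% at 104 per arm only if the ablation rate is about 5.8% or lower. Handle the two resection rates separately as a citation check.

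No extra patients and no change in conduct are asked for. The cost is revised text in the protocol and analysis plan and a less favourable stated power. The trial is ongoing with no interim analysis planned, so the interval can be fixed before outcome results by arm are known.

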### Study Procedures

#### Resection (Standard)

Resection can be performed as laparoscopic surgery, robot-assisted surgery, open surgery, or a combination of these techniques. An adequate resection margin is considered to be more than 1 mm of healthy liver tissue on the resected tumor, except in cases where the tumor is divested from a vessel, so called “R1 vascular”. The resections will be performed using the technique preferred by the responsible surgeon. Parenchyma transection will most frequently be performed using ultrasound guidance and a bipolar sealer transection technique assisted by ultrasonic aspirators and endo-staplers if needed.

#### Ablation (Intervention)

Ablation can be performed percutaneously, laparoscopically, with robotic assistance, through an open approach, or a combination of these techniques. Needle placement is guided by either computed tomography or ultrasound. Microwave ablation is preferred, although radiofrequency ablation is acceptable. All procedures are conducted under general anesthesia.

### Ablation Confirmation

Perioperative CT scanning will be performed in all patients randomly assigned to ablation. A CT scan will be performed with the patient in general anesthesia and with the patient positioned for the ablation procedure. Another CT scan will be performed after completion of ablation, and ablation margins will be evaluated intraoperatively using ablation confirmation software. We aim to achieve an ablation margin of 10 mm, but a margin of minimum 5 mm will be accepted. The exceptions to this are cases where the ablated tumor is close to a vessel, where the adequate margin must be a matter of individual judgement and sometimes may be less than 5 mm.

CT scanning for confirmation of ablation margin can be performed later during the same in-patient visit if renal function or other medical reason prohibits additional intraoperative contrast enhanced CT scanning, or if laparoscopic ablation is performed in an operating room without CT. If insufficient ablation margin is detected, defined as above, re-ablation should be performed within 1 week.

